|-------------------------------------|------------------------------------------------------------------------------------------------------------------------------------------------------------------------------------------------------------------------------------------------------------------------------------------------------------------------------------------------------------------------------------------------------------------------------------------------------------------------------------------------------------------------------------------------------------------------------------------------------------------------------------------------------------------------------------------------------------------------------------------------------------------------------------------------------------------------------------------------------------------------------------------------------------------------------------------------------------------------------------------------------------------------------------------------------------------------------------------------------------------------------------------------------------------------------------------------------------------------------------------------------------------------------------------------------------------------------------------------------------------------------------------------------------------------------------------------------------------------------------------------------------------------------------------------------------------------------------------------------------------------------------------------------------------------------------------------------------------------------------------------------------------------------------------------------------------------------------------------------------------------------------------------------------------------------------------------------------------------------------------------------------------------------------------------------------------------------------------------------------------------------------------------------------------------------------------------------------------------------------------------------------------------------------------------------------------------------------------------------------------------------------------------------------------------------------------------------------------------------------------------------------------------------------------------------------------------------------------------------------------------------------------------|
| Measurements and procedures: | 
Screening will be done every day (Monday to Friday). Eligible patients will be randomly allocated to either intervention or control group. Before inclusion, all patients will be treated according to the ICU- Geneva Protocols.
 
Collected data:
 
Baseline at study inclusion day
 
 
- Body mass, height and body mass index (BMI)
 
- Age, gender
 
- Date and time of admission in the ICU
 
- Primary diagnostic
 
- Known chronic illness (diabetes, acute kidney injury (AKI), pancreatitis, tumor, etc.).
 
- Medication influencing glycaemia (oral antidiabetics' insulin, steroids, prednisone, etc.).
 
- Renal and hepatic status
 
- Glycaemia and lactate
 
- Vitals
 
- Severity score (APACHE II, SAPS II) at ICU admission
 
 
Daily data from inclusion day (maximum follow up of 15 days)
 
When possible – Following routines measurement.
 
 
- Glucose measurements
 
- Other laboratory: lactate, CRP, sodium (Na), potassium (K), glycohemoglobin (HbA1C), urea, creatinine, glomerular filtration rate (GFR), protein, albumin, ASAT, ALAT, phosphatase alkaline, γ-glutamyltranspeptidase (GGT), bilirubin
 
- Any events (intubation, extubation, length of surgery, infusions, cardiac events, infections, requirement for red blood cell (RBC) transfusion, hemodynamic rate (HR), organ failure)
 
- Vitals (blood pressure, temperature, heart rate etc.)
 
- Antibiotics usage
 
- Vasopressor
 
- Steroids
 
- Propofol® for sedation
 
- Glucose perfusion
 
- Insulin therapy including boluses.
 
- Body weight, BMI, Ideal body weight (if needed), presence of oedema.
 
- Energy expenditure (IC or predictive formula)
 
- Energy and protein targets over the day
 
- Prescription and administration (ml of product, kcal and grams of protein).
 
- Daily water balance
 
- Diuresis
 
- Diarrhoea, constipation
 
- Nausea, Vomiting, gastric residual
 
- Physical therapy
 
- Medical Research Council Scale (MRC Scale)
 
 
Upon ICU leave
 
 
- Duration of ICU stay
 
- MRC Scale at ICU discharge
 
- Alive status at ICU discharge
 
- Duration of hospitalization
 
- Alive status at hospital discharge
 
- BMI at hospital discharge
 
 |
|-------------------------------------|------------------------------------------------------------------------------------------------------------------------------------------------------------------------------------------------------------------------------------------------------------------------------------------------------------------------------------------------------------------------------------------------------------------------------------------------------------------------------------------------------------------------------------------------------------------------------------------------------------------------------------------------------------------------------------------------------------------------------------------------------------------------------------------------------------------------------------------------------------------------------------------------------------------------------------------------------------------------------------------------------------------------------------------------------------------------------------------------------------------------------------------------------------------------------------------------------------------------------------------------------------------------------------------------------------------------------------------------------------------------------------------------------------------------------------------------------------------------------------------------------------------------------------------------------------------------------------------------------------------------------------------------------------------------------------------------------------------------------------------------------------------------------------------------------------------------------------------------------------------------------------------------------------------------------------------------------------------------------------------------------------------------------------------------------------------------------------------------------------------------------------------------------------------------------------------------------------------------------------------------------------------------------------------------------------------------------------------------------------------------------------------------------------------------------------------------------------------------------------------------------------------------------------------------------------------------------------------------------------------------------------------------|

|                                              |                                                                                                                                                                                                                                                                                                                                                                                                                                                                                                                                                                                                                                                                                                                                                                                                                                                                                                                                                         |
|----------------------------------------------|---------------------------------------------------------------------------------------------------------------------------------------------------------------------------------------------------------------------------------------------------------------------------------------------------------------------------------------------------------------------------------------------------------------------------------------------------------------------------------------------------------------------------------------------------------------------------------------------------------------------------------------------------------------------------------------------------------------------------------------------------------------------------------------------------------------------------------------------------------------------------------------------------------------------------------------------------------|
| Intervention:                         | 
Intervention group: number of patients: 71.
 
Glucosafe 2 software is used for 15 days or until the patient is discharged from the ICU or starts eating (oral feeding). Glucosafe 2 integrates the following data: body weight (BW), age, gender, type of diabetes, renal replacement therapy, serial blood glucose measurements, insulin therapy and the nutrition support (including non-nutritional calories). Based on those data and according to the mathematical model it contains, Glucosafe 2 will calculate patients' insulin sensitivity and will recommend the dose of insulin and nutrition required for each ICU patient. For more information, see point 8.1.1.
                                                                                                                                                                                                                                                |
| Control intervention (if applicable): | 
Control group: number of patients: 71.
 
Standard care according to department (ICU-HUG) protocol. BG measurement will be made every 2 hours for all patients admitted in the ICU. Depending on the stability of those measurements, BG control will be made in a close or extended way according to our internal protocol.
 
Early enteral nutrition will be started within 48 hours if the medical situation allows it. Nutrition will be given in a progressive way with the aim of covering the energy and protein needs at the end of day 3. For more information, see point 8.1.2.
 
Historical control group: number of patients: 71.
 
Retrospective data, with standard care before the beginning of the pilot study. Historical controls data will be retrospectively collected from the patients' computerized record. They will be recruited within 2 years before the trial starts.
 |
| Number of subjects with rationale:    | Based on data collected routinely at the ICU between January and March 2017, the time in target was 68% (SD 21%) for patients under the standard of care. Considering an improvement of 10% of time in target as clinically important, we would need 71 patients by arm (213 in total) to detect such an effect with a study power of 80% and an alpha error of 5% (two-sided).                                                                                                                                                                                                                                                                                                                                                                                                                                                                                                                                                                         |
| Duration of the investigation:        | 12 months                                                                                                                                                                                                                                                                                                                                                                                                                                                                                                                                                                                                                                                                                                                                                                                                                                                                                                                                               |

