### **3. BACKGROUND AND RATIONALE**

#### **3.1 Background and Rationale for the clinical investigation**

The survival and the outcomes of critically ill patients are strongly influenced by the management of insulin therapy and the nutritional support. All improvements in these care processes and specific therapeutic interventions result in a decreased ICU morbidity and mortality rate [9-11]. Hypo- or hyperglycaemia are related to higher mortality, especially in non-diabetic patients [12, 13]. An association between high blood glucose (BG) variability and increased infection rates and mortality were also observed [14, 15]. In addition, inadequate nutritional support may also contribute to protein loss and muscle wasting, which may lead to post-ICU weakness [16-18] and to a further increase of the ICU and post-ICU morbi-mortality [19-21]. These ICU neuromuscular complications worsen the general clinical outcomes, and are linked to an increased mortality, persistent functional limitations, and cognitive impairment. The reported incidence varies between 25 and 100% [6].

International professional societies have published evidence-based guidelines for BG control and nutritional support for ICU patients [22-24], but their implementation and the adherence to local guidelines remains very challenging. Implementing BG control to local guidelines showed a low 50% adherence [25, 26] and despite nutritional recommendations, patients staying more than 72 hours in the ICU observed in a multicenter study received on average less than 60% of their estimated energy expenditure [27].

The Glucosafe 2 (GS2) software is a decision support system intended to help caregivers in achieving optimised BG control coupled to nutritional support. It is based on a mathematical model of the glucose-insulin metabolism. This model integrates the following data: body mass (BM), age, gender, type of diabetes, renal replacement therapy, serial blood glucose measurements, insulin therapy and the nutrition support (including non-nutritional calories). Based on these data, GS2 can calculate the patient's insulin sensitivity and recommends the dose of insulin and nutrition required for each ICU patient.

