### 9.2.2 Assessment of secondary outcomes

Glycaemic “variability”:

Mean and SD of BG

- All BG measurement will be reported in the eCRF daily. The mean BG with SD will be calculated from those data.
- Maximum of daily BG difference

Achievement of nutritional targets.

The protein goal is met (e.g., 80-100% of the accumulated target)

- In the control group, the total intake of protein per day is going to be reported in the eCRF. Then, it is going to be compared with the daily target and the percentage will be made. The mean percentage for the duration of the study will then be calculated.
- In the intervention group, the comparison between the daily intake and the daily target is carried out automatically by GS2. The percentage will be reported directly in the eCRF. The mean percentage for the duration of the study will when be calculated.

The caloric goal is met (e.g., 80-100% of the accumulated target)

- In the control group, the total intake of energy per day is going to be report in the eCRF. Then, it is going to be compared with the daily target and the percentage will be made. The mean percentage for the duration of the study will when be calculated.
- In the intervention group, the comparison between the daily intake and the daily target will be made automatically by GS2. The percentage will be directly report in the eCRF. The mean percentage for the duration of the study will then be calculated.

Energy debt at the end of the stay

- In the control group, the total intake of energy per day is going to be reported in the eCRF. The daily energy target will be reported every day as well. Then the total energy debt is calculated as the addition of the daily difference between the energy target and the energy intake.
- In the intervention group, the energy debt will be directly calculated and extracted from GS2.

Protein debt at the end of the stay.

- In the control group, the total intake of protein per day is going to be reported in the eCRF. The daily protein target will be reported every day as well. Then, the total protein debt will be calculated as the addition of the daily difference between the protein target and the protein intake.
- In the intervention group, the protein debt will be directly calculated and extracted from GS2.

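### Section 9.2.2 derives energy intake, percentage of caloric target and energy debt differently by arm and does not fix whether non-nutritional calories count in each, so intake may be counted unequally

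*Protocol*

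**What the plan says.** **GS2 inputs.** The Synopsis (Intervention) lists among the data GS2 integrates "serial blood glucose measurements, insulin therapy and the nutrition support (including non-nutritional calories". Section 3.1 repeats this: "insulin therapy and the nutrition support (including non-nutritional calories". Both sentences describe what feeds the model.

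**Intervention arm, Section 9.2.2.** For the caloric goal, "the comparison between the daily intake and the daily target will be made automatically by GS2", and the resulting percentage goes straight into the eCRF. For debt, "In the intervention group, the energy debt will be directly calculated and extracted from GS2".

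**Control arm, Section 9.2.2.** For the caloric goal, "In the control group, the total intake of energy per day is going to be report in the eCRF", after which it is compared with the daily target. For debt, "In the control group, the total intake of energy per day is going to be reported in the eCRF", and then "the total energy debt is calculated as the addition of the daily difference between the energy target and the energy intake".

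**Historical group.** Section 9.2.2 gives no route for its energy outcomes, although Section 11.4.1 compares the intervention group with it.

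**Daily data list.** The Synopsis (Measurements and procedures) has one nutrition item, "Prescription and administration (ml of product, kcal and grams of protein". Propofol and glucose perfusion stand on their own lines with no conversion to kcal. The list is not arm-specific.

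**Outcome definition.** Section 5.2 counts the caloric target as reached on a day when intake is 80–100% of target. It defines energy debt from caloric intake without naming the components of intake.

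**The concern.** Limiting the cumulated energy debt and reaching the daily energy target are part of the secondary objective in Section 4.3. For both, the plan prescribes a calculation by the device under test in one arm and a separately reported total in the other. The trial is unblinded, and Section 8.1.1 has only intervention patients created in GS2, so no control patient passes through the same calculation.

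Non-nutritional calories are mentioned only in connection with GS2. If its output counts them and the control total does not, two patients given the same feed, propofol and glucose would be scored differently because of their arm. Randomisation and a larger sample do not remove a measurement difference of that kind. In intake and debt it would look like better feeding under GS2.

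**Working it through.** **1. What the text settles and leaves open**

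| Item | Intervention | Control | Historical |
|---|---|---|---|
| Source of intake, percentage and debt | Calculated by GS2 | Daily eCRF total, then derived | Not stated |
| Non-nutritional calories | Named as a model input; not stated for the exported values | Not mentioned | Not mentioned |

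The difference in route is stated. The difference in content is possible but not stated.

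**2. Inputs for the size**

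- Example energy expenditure 2160 kcal/day and acuteness factor 70% (Section 8.1.1). The caloric target there reproduces: 2160 × 0.70 = 1512 kcal/day.
- Maximum follow-up 15 days (Synopsis).
- Goal band 80–100% of target (Section 5.2).
- x, the kcal/day counted by GS2 but not in the control total. The documents give no figure. I assume 50–400 for illustration and show 0 as well.

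**3. Debt**

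Take identical patients with daily target T and product intake P, followed for d days.

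- Control debt = d × (T − P)
- GS2 debt = d × (T − P − x)
- Gap = d × x, whatever T is, provided T is the same in both arms

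At d = 15 the gap is 750 kcal for x = 50 (15 × 50) and 6000 kcal for x = 400 (15 × 400). Shorter follow-up shrinks it in proportion: at 3 days it is 150–1200 kcal.

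**4. Percentage of target and the goal band**

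The denominator for goal attainment is the target, 1512 kcal/day in the example, not the expenditure. A patient at 75% or 95% from product alone moves to 75% + x/1512 or 95% + x/1512.

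| x (kcal/day) | 15x (kcal) | x/2160 | x/1512 | 75% becomes | 95% becomes |
|---|---|---|---|---|---|
| 0 | 0 | 0% | 0% | 75.0% | 95.0% |
| 50 | 750 | 2.3% | 3.3% | 78.3% | 98.3% |
| 100 | 1500 | 4.6% | 6.6% | 81.6% | 101.6% |
| 200 | 3000 | 9.3% | 13.2% | 88.2% | 108.2% |
| 400 | 6000 | 18.5% | 26.5% | 101.5% | 121.5% |

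The same 0.05 × 1512 = 75.6 kcal/day lifts a patient from 75% to 80%, into the band, and from 95% to 100%, its upper edge. Anything beyond that takes the second patient out. At x = 400 even the patient at 75% overshoots. Extra counted calories can therefore make goal attainment look better or worse under GS2.

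Where the target equals an expenditure of 2160 kcal/day, moving from 75% to 80% takes 0.05 × 2160 = 108 kcal/day, so x = 100 falls just short at 79.6%.

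**The case against.** A reader might infer that the control total is built from product kcal alone, that GS2's exported debt includes propofol and glucose, and hence that GS2 is bound to look better. The documents do not support that chain.

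- Section 9.2.2 speaks of total energy intake in the control arm, which could include every source. It never names the product line of the daily data list as the source of that total.
- The daily list serves both arms. Separate lines for propofol and glucose are equally consistent with gathering what a complete total needs.
- The phrase on non-nutritional calories describes model inputs. No sentence says that the exported percentage or debt counts them.
- The Section 5.2 definitions do not define intake differently by arm.
- Even if the counting does differ, the 100% cap means that goal attainment need not favour GS2.

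All of this stands, and it limits the point to a possible difference of unknown size.

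It can also be said that the components of a derived variable belong in the SAP or the eCRF specification, neither of which was available here. That would answer mere silence about components. It does not answer the arm-specific calculation, which Section 9.2.2 itself lays down and which an SAP using one common source would have to depart from.

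**Conclusion.** The point holds as an unsecured comparison, not as a demonstrated bias. The protocol fixes different routes to the energy outcomes in the two randomised arms, gives none for the historical group, and leaves open whether propofol and glucose energy is counted alike.

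If GS2 counts x kcal/day more than the control total, intake is overstated by x per day and debt understated by x per day under GS2, relative to control. Over 15 days that is 750–6000 kcal for x between 50 and 400. This rests on an assumed x, on such calories being given every day and on the maximum follow-up. The gap is zero if both arms count the same items. The direction is fixed for intake and debt but not for goal attainment. Only secondary outcomes are touched.

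**What to change.** In Section 9.2.2, define one energy-intake variable for all three groups: enteral product kcal + parenteral product kcal + propofol lipid kcal + glucose-infusion kcal. Derive it for every patient, including those in the GS2 arm, from the same daily fields. Use it for the between-group comparisons of percentage of caloric target and of energy debt. Keep the GS2-calculated values as descriptive results or as a sensitivity check.

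The rewrite should also settle a neighbouring mismatch: Section 5.2 defines energy debt from energy expenditure, whereas Section 9.2.2 calculates the control debt from the energy target.

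The cost is one derivation rule and a little programming, since product, propofol and glucose are already on the daily list. The Synopsis only names the last two, so the eCRFs, including the retrospective one, should be checked for the amounts needed to convert them to kcal. Nothing changes in treatment, the primary outcome or the sample size.
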